#### Blinding

Given the nature of the intervention, the participating subjects will not be blinded. However, to minimise any contamination between groups, the investigator responsible for the measurements of the study at each assessment and for the statistical analysis will be blinded, thus increasing the scientific quality in the study process.

### Procedures and data collection

#### Evaluations and study plan

Three assessments will be completed in this study: one at the beginning, another after 7 days, and a final one before the patient is discharged from hospital. After recruitment and before randomisation and assignment to the corresponding group, all individuals will complete a baseline assessment (BA), which includes recording the independent variables and the variables of the primary and secondary results of the study. Then, while the patients are still in hospital, the subjects will be randomly assigned to the control or the experimental group, with the corresponding intervention applied in each of them. Later, two more assessments will be completed, one after 7 days, considered to be the follow-up assessment (FUA), and another at the time of discharge from the hospital, considered to be the final assessment (FA). This can be observed in more detail in Table 1.

**Table 1 Tab1:**
[figure not shown]
Timeline and dimensions assessed at the time points

#### Description of the variables

For the principal variable being manipulated, we will study dyspnoea (Medical Research Council, MRC) and the degree of dependence in carrying out the activities of daily living (Barthel Index, BI). And as secondary variables, we have the patient’s physical performance (via the Short Physical Performance Score, SPPB), their fear/avoidance of movement (Tampa Scale of Kinesiophobia–Fatigue, TSK-F), the oxygen saturation in the blood (pulse oximetry), and the quality of life of the oncology patient (ECOG performance status scale). Other intervening variables include those gathered from the patient’s clinical history, such as pathological diagnosis, number of lines of treatment, and socio-demographic and anthropometric data (sex, age, weight, height, and BMI).

#### Tools employed in the evaluation of the variables

“Barthel Index, (BI)” [18]: to evaluate dependence. Measures physical disability with proven validity and reliability. It is easy to apply and to interpret. Useful for evaluating the patient’s functional independence in the activities of daily living (ADL). Scored from 0 to 100, it quantifies the individual’s degree of dependence.“Medical Research Council dyspnoea scale (MRC)” [19], to evaluate dyspnoea. The aim is to make it possible for the patients to quantitatively grade their own dyspnoea in a simple, visual manner. It establishes 5 degrees of dyspnoea when carrying out activities.“Short Physical Performance Score (SPPB)” [20], to evaluate physical performance. The short physical performance battery, proven in our area for primary health care, is a test designed specifically to predict disabilities, and it has demonstrated the capacity to predict adverse events, dependence, institutionalisation, and mortality.The “Tampa Scale of Kinesiophobia–Fatigue (TSK-F)” [8, 9], was developed to evaluate the fear of movement related to fatigue/pain. It has been proven effective in oncology patients and those with chronic fatigue syndrome. We will use the model with 11 items (TSK-F-11).“Pulse oximetry” [21]: a non-invasive technique which uses a pulse oximeter to measure the saturation of oxygen (Sat O_2_) in the haemoglobin in circulating blood, usually in arterial blood.“ECOG performance status scale” [22], is a practical way to measure the quality of life of cancer patients, whose life expectancies may change within a period of months, weeks, or even days. It was designed by the Eastern Cooperative Oncology Group (ECOG) in the United States and validated by the World Health Organization (WHO). The primary function of this scale is to objectify the patient’s quality of life or performance status.

The variables will be recorded on an individual sheet for each patient and stored afterwards in a database designed specifically for this study.

#### Interventions

The conventional standard of care will be maintained in both groups, as well as the lines of treatment prescribed by the Medical Oncology Service of the CAUSA. Additionally, all subjects in both groups will receive an individualised prescription of multimodal physical exercise.

In the experimental group, we will also implement an intervention with a programme for recovering the individual’s autonomy by means of reeducation in the activities of daily living.

The *oncological functional reeducation programme* will comprise the following actions:
Multimodal physical exercise programme: this therapeutic measure will be applied for all individuals, in both the experimental group and the control group. It will consist of two short sessions each day, one in the morning and another in the afternoon, of 15–20 min each. The dose and load of the programme, as well as any special considerations, will always be adapted to the functional capacities of each patient, in accordance with the assessments carried out. Additionally, we will always take into consideration the patient’s symptoms at the time, as there may be individual changes in a very short period of time. The directive will be to maintain a multimodal exercise programme to complete different exercises, including aerobic exercises, balance exercises, and low-load resistance training exercises targeting specific muscle groups, in both the upper quadrant and the lower quadrant. The sessions will be done following the recommendations of the American College of Sports Medicine (ACSM) [23], with an initial warm-up (2–3 min), a main part (8–12 min), and a final cool-down and relaxation (5 min)It will be permitted—and recommended—to do the exercises with the patient’s specific oxygen therapy range, if they have one. The patient’s oxygen saturation levels will also be measured before, during, and after completing the exercise, to ensure that there are no clinical alterations, which may contraindicate the therapeutic practice.Reeducation in the activities of daily living: Intensity and simplification of the activities and trainings of energy-saving techniques (EST). An individual training will be completed on the rules for the simplification of activities, consisting of [24]:
Exhaustive organisation of the workspaces where the activities are to be carried outAdaptation of the work plans and placement of the objects within the patient’s reachPrioritising basic self-care activities while sittingMovement control: doing the movements in a slow, coordinated, and harmonious manner, avoiding impulsive and vigorous movementsAlternating heavy activities with light activities, establishing the required rest times between themCombining periods of balanced activity with periods of restAn individualised assessment will also be completed where we will prescribe the support products which will facilitate the patient’s mobilisation when completing their activities of daily living, such as a walker with an adaptation for oxygen therapy (a portable oxygen concentrator).And finally, we will complete an exhaustive daily log of the activity that the patient does, which we will in turn use to modify the same activity, adapting it to the patient’s clinical situation at all times. In this way, we will establish a proper pattern, which will lead the patient to improve their autonomy, as they will be using all of their capacities available at the time, without exceeding them or discounting them. This will be done using a diary which the patient will complete each day and which the investigator responsible for the intervention will supervise daily.

### Data analysis

The statistical analysis will be carried out with the intention to treat. In the descriptive analysis, the population is described by presenting the data as means and standard deviations for the continuous variables and as frequency distributions for the qualitative variables. To evaluate the comparability in the baseline assessment between the two study groups, we will employ the Chi-squared test for qualitative variables and the Student’s T-test for the comparison of the means between the two groups, in addition to the Kolmogorov–Smirnov test to find the normality of the sample. In the inferential analysis, we will consider a confidence interval of 95% (*p* < 0.05), and will use Student’s T-test for related pre and post samples and for independent samples at the end of the study, in addition to a multivariate analysis of variance (MANOVA) with repeated measures (3 levels) to assess interactions between categorical variables, and to determine significant differences between groups and within groups. Additionally, to assess the magnitude of the change in the variables, the effect size of the interventions will be calculated as Cohen’s d (small (0.2), medium (0.5), and large (0.8)) and the partial eta squared (ƞ2p) (small (0.01), medium (0.06), and large (0.14)), where significant, as appropriate with the statistical test applied [25]. We will use Pearson’s Correlation Coefficient to analyse the correlations between the various intervening variables and the parameters established in the different questionnaires and scales employed. A survival follow-up analysis will be completed using the Kaplan–Meier non-parametric method to learn the time of the intervention until the patient’s discharge from hospital, and the survival curves of each of the groups in the study will be compared using the non-parametric logrank test. Processing and analysing the data will be done using the statistics pack SPSS 25.0.

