### Sample/participants

#### Participants

The patients will be recruited from the Oncology Hospitalisation Unit at the CAUSA, and must meet the following selection criteria: A) Inclusion criteria: Participants must have a pathological diagnosis of an oncological disease, be over 18 years of age, be hospitalised at the time of recruitment in the Oncology Unit at CAUSA, meet dyspnoea parameters of 2 or more points on the Medical Research Council scale (MRC), receive fewer than 85 points on the Barthel Index, and have signed an informed consent form indicating voluntary agreement to participate in the study. B) Exclusion criteria: not having an adequate cognitive state to be able to comprehend and follow the orders provided (fewer than 23 points on the Mini Mental State Examination, MMSE), having a haemoglobin level lower than 10 g/dL, being an active smoker at the time of recruitment. C) Withdrawal criteria: disease progression which brings the patient to a terminal situation or to death, and non-completion of the follow-up and final assessments.

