#### Sample size

The sample size has been estimated based on the potential modification of the most stringent of the principal variables of the study—the score on the Barthel Index. For this, as a reference, we have used the results obtained in a study with similar characteristics, in which the scoring on the Barthel Index was modified by 7.5 points [17]. With these premises, accepting an alpha risk of 0.05 and a beta risk of 0.2 in a bilateral contrast, we will need 25 subjects in the first group and 25 subjects in the second group in order to detect a difference greater than or equal to 7.5 units. The assumed common standard deviation is 8.3. We estimate a rate of 20% lost to follow-up. The sample size was estimated using the programme EPIDAT 4.2.

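### None of the planned between-arm analyses adjusts the final Barthel score for the baseline that is already collected; an ANCOVA would be more powerful at any useful baseline-end correlation

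*Protocol article*

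**What the plan says.** **Analysis.** The Data analysis section of the protocol article lists the inferential tests in one sentence: Student's "T-test for related pre and post samples and for independent samples at the end of the study", and in addition a repeated-measures MANOVA with three levels, meant for interactions and for differences between and within groups. No test is designated primary. Baseline values otherwise serve only to check that the groups are comparable.

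**Baseline.** Under Evaluations and study plan, both primary outcomes are recorded for everyone before randomisation, and again at day 7 and at discharge. The Participants section limits entry to patients who "receive fewer than 85 points on the Barthel Index".

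**Sample size.** "The sample size has been estimated based on the potential modification of the most stringent of the principal variables of the study", namely the Barthel Index. The reference is a study in which "the scoring on the Barthel Index was modified by 7.5 points". The calculation proceeds "accepting an alpha risk of 0.05 and a beta risk of 0.2 in a bilateral contrast", to "detect a difference greater than or equal to 7.5 units", with 25 patients per group and 20% loss. "The assumed common standard deviation is 8.3"; the section does not say whether this is the SD of end scores or of change.

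**The concern.** In a randomised trial of this size, the baseline value of a functional score is usually the best available predictor of its final value. An independent-samples t-test on final scores leaves that information out. The predictable part of the variation stays in the error term, and any chance baseline difference between arms passes partly into the estimate. The MANOVA does use baseline, but as an outcome level: its group-by-time interaction is a two-degree-of-freedom test of change, not an adjusted mean difference at discharge.

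Two further features add to this. The sample-size wording points towards change, while the end-of-study test uses raw scores. If 8.3 is the SD of change, raw scores have a larger SD whenever the baseline-end correlation exceeds 0.5. Also, the paired pre-post tests sit among the inferential analyses at p < 0.05. Patients are selected for low Barthel scores and both arms exercise, so improvement in both arms is plausible whether or not the added programme works.

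At stake are the precision of the main result, the stated 80% power under one reading of the SD, and clarity about which result answers the between-arm question.

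**Working it through.** **Inputs from the Sample size section:** two-sided alpha 0.05, power 0.80, difference 7.5, SD 8.3, 25 per group, 20% loss. **Assumed, because the article does not give it:** the baseline-end correlation ρ, taken as 0.3 to 0.8, with equal SDs at baseline and end.

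**1. Reproducing the plan's figure.** n per arm = 2 × [8.3 × (1.960 + 0.842) / 7.5]² = 19.2, rounded up to 20; 20 / 0.8 = 25. This matches the article. The sizing is therefore that of an unadjusted two-group comparison with SD 8.3. At 20 completers per arm its power is 81.5% by the normal formula and 79.5% by the noncentral t, which is used below.

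**2. Formulas.**
- ANCOVA residual SD = SD(end) × √(1 − ρ²), with 37 degrees of freedom instead of 38.
- If 8.3 is the SD of change, SD(end) = 8.3 / √(2(1 − ρ)).

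**3. Reading A: 8.3 is the SD of end scores** (20 per arm, difference 7.5).

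| ρ | End-score t-test | ANCOVA residual SD | ANCOVA power |
|---|---|---|---|
| 0.3 | 79.5% | 7.92 | 83.1% |
| 0.5 | 79.5% | 7.19 | 89.5% |
| 0.7 | 79.5% | 5.93 | 97.4% |
| 0.8 | 79.5% | 4.98 | 99.6% |

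**4. Reading B: 8.3 is the SD of change.**

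| ρ | SD(end) | End-score t-test | ANCOVA residual SD | ANCOVA power |
|---|---|---|---|---|
| 0.3 | 7.01 | 90.9% | 6.69 | 93.2% |
| 0.5 | 8.30 | 79.5% | 7.19 | 89.5% |
| 0.7 | 10.72 | 57.8% | 7.65 | 85.5% |
| 0.8 | 13.12 | 42.1% | 7.87 | 83.5% |

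With no losses at all (25 per arm), the t-test under reading B would still have only 67.9% at ρ = 0.7 and 50.8% at ρ = 0.8.

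**5. The MANOVA interaction.** This is an F test with 2 and 37 degrees of freedom on the changes from baseline to day 7 and to discharge. Compound symmetry is assumed, so the two changes correlate 0.5. Under reading B, if the benefit builds linearly (3.75 at day 7, 7.5 at discharge), the noncentrality is 8.17 and power 69%. If the full 7.5 is present by day 7, the noncentrality is 10.89 and power 82%. Neither depends on ρ under this reading. Under reading A at ρ = 0.8, the MANOVA has 98% or more and is practically level with ANCOVA.

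**6. Within-arm paired tests.** Suppose both arms have the same true gain, the SD of change is 8.3 (assumed) and there are 20 per arm. If each test is significant with probability p, exactly one of the two is significant with probability 2p(1 − p).

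| True gain in both arms | p | One significant, the other not |
|---|---|---|
| 2 | 17.6% | 29% |
| 4 | 53.4% | 50% |
| 6 | 86.6% | 23% |
| 7.5 | 96.9% | 6% |

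The 4-point row is close to the mathematical maximum of 50%, so it should be read as an upper end.

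**The case against.** **Baseline is not ignored.** A reader might infer that the plan makes no use of baseline Barthel in comparing the arms. The documents do not support that: the MANOVA covers all three assessments, and its interaction compares change between arms. This stands. What remains is that it does not give a baseline-adjusted difference at discharge, and that in several of the scenarios above it has less power than ANCOVA.

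**The t-test is not invalid, and the trial is not shown to be underpowered.** Randomisation makes the unadjusted comparison valid. The end-score t-test is one of several listed tests, and under reading A it has essentially its planned power. Even under reading B there is no shortfall at ρ = 0.3 and practically none at 0.5. The Barthel limit at entry may also lower ρ by narrowing the baseline range. All of this stands.

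**Sizing on change is not certain.** The wording about modification of the score suggests it, but the SD is unlabelled and the formula suits either reading. Hence both are shown.

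**Nothing says that the paired tests will be read as a treatment effect.** True: between-group tests are planned alongside them. The risk is one of interpretation, and its size depends strongly on an assumed gain.

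**Covariates are often left to an SAP.** Also true, and the SAP is not shown. But the article does not leave the method open: it names its tests, and an independent-samples t-test has no covariate. A stated choice can be judged.

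**Conclusion.** The point holds as an improvement to a stated analysis, not as an error that invalidates the trial. No listed analysis adjusts final Barthel for its baseline, although that baseline is collected before randomisation. ANCOVA has higher power than the end-score t-test at every correlation from 0.3 to 0.8. The gain is about 4 to 20 percentage points if 8.3 is the SD of end scores, and about 2 to 41 points if it is the SD of change. Only under the change reading with ρ above about 0.5 does the t-test fall clearly below the stated 80%; ANCOVA stays above 83% throughout.

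The within-arm tests cannot answer the between-arm question. With equal true gains of 4 to 7.5 points they would give conflicting results in about 50% down to 6% of trials.

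These figures rest on 20 completers per arm, approximate normality, equal SDs over time and an assumed ρ. If ρ is near zero the gain disappears: under reading A at ρ = 0, power is 79.5% with either method.

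**What to change.** - In Data analysis, name one primary between-arm analysis of the final Barthel score: an ANCOVA on arm with baseline Barthel as covariate, or an equivalent mixed model. Report the adjusted mean difference with its 95% CI.
- Use the same model for SPPB, TSK-F and oxygen saturation, each with its own baseline.
- Report within-arm pre-post changes descriptively, without p-values.
- In Sample size, state whether 8.3 is the SD of end scores or of change.

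The cost is one degree of freedom and a change of wording. No further data or patients are needed.

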**Methods:**

This is a protocol por an experimental, prospective, randomized, parallel-controlled clinical trial, with two arms design of fixed assignment with an experimental and control groups. It will conduct in the Oncology Hospitalisation Unit at the University Hospital Complex of Salamanca, using consecutive sampling to select 50 participants with oncological dyspnoea who are hospitalised at the time of inclusion. After baseline assessment, participants will be randomised into the groups. Experimental group will complete Comprehensive Rehabilitation with the autonomy recovery and the multimodal exercise programmes, and in the control group, only the multimodal exercise programme will be carried out. The primary outcomes will be basic activities of daily living (Barthel Index) and degree of dyspnoea (MRC scale). Additionally, physical performance will be evaluated with the Short Physical Performance Battery (SPPB), as will the oxygen saturation in the blood using pulse oximetry, fear/avoidance of movement with the Tampa Scale of Kinesiophobia (TSK), and the quality of life of the oncology patient (ECOG performance scale).

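### MRC dyspnoea, a five-grade primary outcome, is compared between arms only through means and Cohen's d, and the end-of-study t-test ignores baseline grade; pre-specify one baseline-adjusted ordinal comparison

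*Protocol article*

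**What the plan says.** The abstract of the protocol article names two primary outcomes: "The primary outcomes will be basic activities of daily living (Barthel Index) and degree of dyspnoea (MRC scale"). The section on tools says of MRC: "It establishes 5 degrees of dyspnoea when carrying out activities", with patients grading themselves. Participants must "meet dyspnoea parameters of 2 or more points on the Medical Research Council scale (MRC"), so at most four of the five grades can occur at entry. MRC is recorded at baseline, at day 7 and before discharge.

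Under Data analysis the post-baseline tests are Student's "T-test for related pre and post samples and for independent samples at the end of the study" and a MANOVA with repeated measures at three levels. Effect sizes are Cohen's d and partial eta squared. Chi-squared appears only for baseline comparability. A Kolmogorov-Smirnov "test to find the normality of the sample" is listed in the same baseline sentence, with no consequence attached. No rank or ordinal method is named for any scale, and the text does not say whether MRC and ECOG count as continuous or qualitative.

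**The concern.** The article does not leave the choice of test open: it names mean-based tests for all outcomes, and it names non-parametric methods only for time to discharge. For MRC this has two consequences.

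- **Interpretation.** A difference in mean grade, or Cohen's d computed on grades, gives one step the same value wherever it occurs on the scale. The article gives no basis for that, and a mean does not show how many patients moved between which grades.
- **Information left unused.** The independent-samples t-test compares end-of-study grades alone, although each patient's baseline grade is known. If baseline and final grades are correlated, this costs precision in a trial of 50 patients.

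At stake are the readability and precision of the result on one of two primary outcomes. Type I error is not at stake.

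**Working it through.** **1. Evaluable patients.** The Sample size section works from "accepting an alpha risk of 0.05 and a beta risk of 0.2 in a bilateral contrast", a Barthel difference of 7.5 and an SD of 8.3.

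n per arm = 2 × (1.960 + 0.842)² × 8.3² / 7.5² = 2 × 7.849 × 68.89 / 56.25 = 19.2, rounded up to 20.

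With 20% loss: 20 / (1 − 0.20) = 25. The stated 25 per arm is reproduced and this point does not change it. About 20 evaluable patients per arm is the setting used below. The article gives no MRC distribution or target effect, so every grade distribution below is an assumption.

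**2. Size of the t-test on five grades.** With no effect, 20 or 25 per arm and 20,000 runs per setting, the t-test rejected in 4.7-5.2% of trials. With 80% of patients in one grade it rejected in 4.0-4.4%. It is not inflated.

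**3. Power, t-test against unadjusted Wilcoxon, 20 per arm.** The first four rows assume a common odds ratio of 4.5. The last two assume that the effect is confined to emptying the most severe grade. Percentages run from the lowest to the highest grade.

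| Control grades (%) | Effect | t-test | Rank test |
|---|---|---|---|
| 10/20/40/20/10 | OR 4.5 | 72.0% | 72.4% |
| 45/30/15/7/3 | OR 4.5 | 57.2% | 62.5% |
| 2/3/5/20/70 | OR 4.5 | 63.4% | 68.3% |
| 80/12/3/2/3 | OR 4.5 | 19.6% | 28.0% |
| 10/30/20/10/30 | to 10/30/50/10/0 | 35% | 23% |
| 40/10/10/10/30 | to 40/30/20/10/0 | 41% | 25% |

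Under proportional odds the rank test is level, or ahead by about 3 to 9 points when grades pile up at one end. (The 9 is the extreme shape at 25 per arm: 34.7 − 25.3 = 9.4.) Under the other two shifts the t-test leads by 35 − 23 = 12 and 41 − 25 = 16 points.

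**4. Baseline adjustment.** In a simulation with 250 runs, 20 per arm and an assumed latent correlation of 0.6 between baseline and follow-up, power was 66% for the end-of-study t-test, 70% for a change score and about 79-80% with baseline adjustment. Almost all of the gain came from the adjustment rather than from the ordinal model. The Monte Carlo standard error of each figure is about √(0.66 × 0.34 / 250) = 3.0 points or √(0.80 × 0.20 / 250) = 2.5 points.

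The order is what theory predicts. Relative to the unadjusted comparison, the variance is 2(1 − 0.6) = 0.80 for a change score and 1 − 0.6² = 0.64 with adjustment. Coarse grading lowers the observed correlation, so the gain on grades is somewhat smaller than these factors imply.

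**5. Kolmogorov-Smirnov on a four-value grade.** With the Lilliefors correction, normality is rejected in 99-100% of samples of 25 or 50. Without it, rejection is 12-42% at n = 25 and 83-100% at n = 50. The article does not say which version applies. If an analyst took whichever of the t-test and rank test was significant, false positives would be 5.6-6.4%.

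**The case against.** The strongest reply is that a t-test with correct size on a five-grade scale is a legitimate choice, that preferring a rank test is taste, and that a condensed article may leave fallback tests to an analysis plan. Much of this stands.

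- A reader might infer that the plan has no suitable test for MRC. It does not follow: the type I error is about 5%.
- A reader might infer that the t-test loses power and a rank test never does worse. That holds only under a common odds ratio, the alternative for which the rank test is well suited. The last two rows of the table reverse it, and the documents do not say which pattern to expect.
- A reader might infer that the normality check will nearly always reject and so lead to a post-hoc change of test. Rejection depends on the version and the sample size, and the article attaches no decision rule to the check. Even opportunistic selection adds only about 1 point.
- The absence of a named fallback is not a finding in a condensed article.
- The MANOVA includes baseline as one of its three levels, so baseline is not wholly unused. Only the end-of-study t-test ignores it. The power of the MANOVA was not simulated.
- A separate small check (250 runs) gave 58% for baseline-adjusted proportional odds against 56% for a baseline-adjusted comparison of mean grades, which is within simulation error. The ordinal model therefore has to be justified by interpretation, not power.
- ECOG is secondary, and the article does not state its number of grades, so no grade-count argument can be made for it from the documents.

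What the reply does not remove is that the article itself fixes mean-based tests and Cohen's d for a graded primary outcome, and that one of the named between-arm tests omits the baseline grade.

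**Conclusion.** The point holds as one of interpretation and efficiency, not validity. The MRC result will be expressed as a mean difference and Cohen's d that assume equal steps, and the end-of-study comparison leaves baseline information unused. Replacing the t-test by an unadjusted rank test would be close to an even trade: roughly 0 to 9 points gained under proportional odds, 12 to 16 lost if the effect is confined to the most severe grade. Baseline adjustment is the more reliable gain, about 79 − 66 = 13 points over the end-of-study t-test and about 9 over a change score in one small simulation. That figure rests on the assumed correlation of 0.6 and would shrink with a weaker one. None of these sizes can be fixed for this trial, because the article gives no MRC distribution, correlation or target effect. It is worth changing because the outcome is primary and the cost is small.

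**What to change.** In Data analysis, pre-specify a single between-arm analysis of MRC: the grade at one named post-baseline visit (the current t-test is placed at the end of the study) compared by arm with adjustment for baseline grade. Use a proportional-odds model, or a Wilcoxon (van Elteren) test stratified by baseline grade if cells are too sparse at about 20 per arm, with the sparseness rule written down in advance. Report the common odds ratio, or the probability of a better grade, with a 95% CI, and the number of patients in each grade by arm and visit. State that the Kolmogorov-Smirnov result does not choose the test. The mean difference may stay as a supporting summary, and ECOG can be handled in the same way.

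The cost is about two sentences, with no new data, patients or visits. There are three downsides: an odds ratio is less familiar to clinical readers, the proportional-odds assumption needs a check, and a mean-based test can have more power if the effect is confined to the extreme grade.

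### The 3-level repeated-measures MANOVA includes the pre-randomisation baseline, so its group main effect understates the treatment difference and should not be read as the between-arm comparison

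*Protocol article*

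**What the plan says.** The Data analysis section lists Student's t-tests (paired, and for independent samples at study end) and, alongside them, the following model: "multivariate analysis of variance (MANOVA) with repeated measures (3 levels) to assess interactions between categorical variables, and to determine significant differences between groups and within" each arm. It does not name the three levels.

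Evaluations and study plan sets exactly three assessments: "one at the beginning, another after 7 days, and a final one before the patient is discharged from hospital". It also fixes when the first takes place: "After recruitment and before randomisation and assignment to the corresponding group, all individuals will complete a baseline assessment (BA"). No other three-level time factor appears in the article, so the pre-randomisation baseline is one of the levels.

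The Sample size section wants enough patients "in order to detect a difference greater than or equal to 7.5 units" on the Barthel Index. It adds: "The assumed common standard deviation is 8.3".

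**The concern.** The stated aim is to show that the autonomy programme adds benefit to exercise alone, so the relevant null is that the arms do not differ after treatment. In a repeated-measures model with three visits, the ordinary between-groups test is the group main effect, which compares each arm's average over all three visits. Randomisation makes the expected arm difference at baseline zero. The test thus averages one null visit with two treated ones and carries the baseline noise as well.

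The sentence gives the model two separate purposes, interactions and differences between groups, and no test is named as decisive. A reader of the results could take a non-significant group main effect as evidence against the added programme, when that test is a diluted version of the question.

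**Working it through.** **Inputs from the Sample size section.** Difference 7.5; SD 8.3; error rates, "accepting an alpha risk of 0.05 and a beta risk of 0.2 in a bilateral contrast"; planned size per arm, "we will need 25 subjects in the first group and 25 subjects in the second group"; attrition, "We estimate a rate of 20% lost to follow-up".

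**Inputs assumed, because the article does not give them.** SD 8.3 is the SD of the score and is the same at every visit. The correlation rho is equal between all pairs of visits, range 0.3 to 0.8. The share f of the discharge effect already present at day 7 is 1, 0.5 or 0. There are 20 completers per arm.

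**Step 1, the plan's own figure.** n per arm = 2 × [8.3 × (1.96 + 0.84) / 7.5]² = 19.2, rounded up to 20. With 20% loss, 20 / 0.8 = 25. The stated 25 per arm is reproduced, and it belongs to a two-sample comparison at one time point. With 20 per arm the exact t-test power is 79.5% (81.5% by the normal approximation).

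**Step 2, size of the main-effect contrast.** Expected difference in the 3-visit mean = (0 + 7.5f + 7.5) / 3.

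- f = 1: 15 / 3 = 5.0
- f = 0.5: 11.25 / 3 = 3.75
- f = 0: 7.5 / 3 = 2.5

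For any f up to 1 the contrast is at most two-thirds of 7.5. This step needs no correlation.

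**Step 3, its standard deviation.** SD of the 3-visit mean = 8.3 × √[(1 + 2rho) / 3]: 6.06 at rho 0.3, 6.78 at 0.5, 7.42 at 0.7 and 7.73 at 0.8. Averaging reduces the SD, but less and less as the correlation rises.

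**Step 4, power of the 3-level group main effect** (noncentral t, 38 df, 20 per arm), against 79.5% for the discharge t-test:

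| Effect at day 7 | rho 0.3 | rho 0.5 | rho 0.7 | rho 0.8 |
|---|---|---|---|---|
| Full (f = 1) | 72% | 62% | 55% | 51% |
| Half (f = 0.5) | 48% | 40% | 34% | 32% |
| None (f = 0) | 25% | 21% | 18% | 17% |

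At very low correlation with the full effect at day 7 nothing is lost: 83.5% at rho 0.1 and 89.5% at rho 0.

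**Step 5, the alternatives under the same assumptions.** The 2-visit mean of day 7 and discharge has contrast (7.5f + 7.5) / 2 and SD 8.3 × √[(1 + rho) / 2]. With baseline as covariate, its variance falls by (8.3 rho)². The interaction is a Hotelling T² on the two changes from baseline. The change contrast has SD 8.3 × √[2(1 − rho)]. The adjusted discharge comparison has SD 8.3 × √(1 − rho²).

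| Test | rho 0.3 | rho 0.5 | rho 0.8 |
|---|---|---|---|
| Day 7 + discharge, f = 1 | 93% | 90% | 84% |
| Day 7 + discharge, f = 0.5 | 74% | 67% | 60% |
| Day 7 + discharge, f = 0 | 41% | 36% | 31% |
| Same, baseline covariate, f = 0.5 | 80% | 84% | 98% |
| Same, baseline covariate, f = 0 | 46% | 50% | 78% |
| Group-by-time interaction, f = 1 or 0 | 67% | 82% | above 99% |
| Group-by-time interaction, f = 0.5 | 54% | 69% | 98% |
| Change to discharge, unadjusted | 65% | 79.5% | 99% |
| Discharge, baseline covariate | 83% | 90% | above 99% |

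Restricting the levels to the two post-randomisation visits beats the 3-level main effect in every row and column. The interaction does not always: at rho 0.3 with f = 1 it has 67% against 72%.

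**The case against.** The strongest reply is that the plan already contains the right test. The same sentence of the Data analysis section provides an independent-samples t-test at the end of the study, and that is the comparison the sample size supports. It also names interactions among the purposes of the MANOVA, and a group-by-time interaction needs baseline as a level, so three levels is an ordinary mixed design. The term group main effect never appears, and which model term decides is often left to an analysis plan that is not shown here.

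Much of this stands, and it rules out three stronger readings that a reader might infer:

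- *A real 7.5-point benefit would usually be missed.* Not for the plan as a whole: the planned discharge t-test finds it about 80% of the time under the plan's own assumptions.
- *The main effect loses about half its power.* That holds only if about half the effect is present at day 7. The article gives neither a day-7 effect nor a correlation, and other assumptions give much smaller or larger losses.
- *A significant change over time would be claimed as success.* The article plans to look at within-group differences, but nowhere treats them as evidence for the added programme.

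What does not stand is the defence by brevity. The article does more than leave the deciding term open: it assigns the detection of differences between groups to a 3-level model. The ordinary test under that label is the diluted one.

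**Conclusion.** The point holds in a limited form. The baseline level reduces the expected group main effect by at least a third, unless the day-7 effect exceeds the discharge effect. This follows from the visit schedule alone.

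The loss of power is conditional. With 20 completers per arm, equal SD 8.3, 7.5 points at discharge and equal correlation of 0.3 to 0.8, main-effect power is 51-72%, 32-48% or 17-25% for a full, half or absent effect at day 7, against about 80% for the discharge t-test. At very low correlation with a full day-7 effect there is no loss. The article does not say whether 8.3 is the SD of the score or of the change; the two coincide at rho 0.5.

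The sample size and the end-of-study t-test are unaffected. The damage is confined to the 3-level group main effect and arises if that term is read as the treatment comparison, which the present wording allows.

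**What to change.** In the Data analysis section, state that the repeated-measures model's between-arm result comes from the post-randomisation visits only (day 7 and discharge as levels, baseline value as covariate), or else from the group-by-time interaction, and that a group main effect over three levels is not read as the treatment comparison. Keep the end-of-study arm comparison, preferably adjusted for baseline, as the test the sample size supports.

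The cost is one or two sentences. Baseline is already collected, so no new data are needed. Three limits should be accepted openly:

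- The 3-level group main effect can no longer be quoted as an efficacy result.
- The average of day 7 and discharge is itself diluted if the effect appears late, so it should accompany the discharge comparison and not replace it.
- An unadjusted change-from-baseline contrast should not replace the discharge comparison either, because it is weaker when the correlation is below 0.5 (65% against 79.5% at rho 0.3).
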